**Figure 1 figure1:**
[figure not shown]
Flowchart of the study design for the group of older adult with mild to moderate depressive symptoms. GDS: Geriatric Depression Scale.

**Figure 2 figure2:**
[figure not shown]
Flowchart of the study design for the group of older adult with moderate to severe depressive symptoms. GDS: Geriatric Depression Scale.

### Participants

#### General Population

Participants with mild to moderate depressive symptoms will be recruited from the general population in the Netherlands. They will be eligible to participate if they (1) are aged at least 55 years, (2) have a Geriatric Depression Scale-15 (GDS-15) score between 5 and 10, (3) are able to work with a computer, and (4) have access to a computer with internet. Candidates will be excluded from the study if they (1) do not have adequate proficiency in the Dutch language or (2) have suicidal thoughts, assessed as having a score of 1 or higher on the 9th item of the Patient Health Questionnaire 9 (PHQ-9) [32]. Having suicidal ideation is considered an exclusion criterion to minimize the risk of an adverse event during the study period.

#### Specialized Mental Health Care Service

Participants with moderate to severe depressive symptoms will be recruited via a specialized mental health care outpatient clinic (Geestelijk gezondheidszorg [GGZ] inGeest, Amsterdam, the Netherlands). Patients who are in treatment at the clinic will be eligible to participate if they (1) are aged at least 55 years, (2) have a GDS-15 score between 8 and 15, (3) are able to work with a computer, and (4) have access to a computer with internet. Candidates will be excluded from the study if they (1) do not have adequate proficiency in the Dutch language or (2) have suicidal thoughts, assessed as having a score of 1 or higher on the 9th item of the PHQ-9 [32]. Having suicidal ideation is considered an exclusion criterion to minimize the risk of an adverse event during the study period.

### Study Intervention: Online Treatment Platform

Moodbuster 2.0 has been developed and tested in a number of European projects. It is an innovative online and mobile solution for the treatment of adult depression and can be applied for research purposes. The platform has a patient and therapist portal (Figure 3) and can be used in unguided, guided, or blended formats and in different settings [33-35]. For the purpose of these studies, Moodbuster 2.0 has been adapted to meet the needs of depressed older adults. To make Moodbuster more aligned with the target group of older adults, the original Moodbuster modules were adjusted by making the content shorter and more relevant to older adults.

**Figure 3 figure3:**
[figure not shown]
Screenshot of the patient portal of Moodbuster 2.0.

Moodbuster 2.0 for older adults consists of 7 web-based CBT modules. These modules are aimed at psychoeducation, behavioral activation, cognitive therapy, problem-solving, exercise, sleep, and relapse prevention. The sleep module is a new addition we have made to the platform; it is aimed at older adults, as insomnia and other sleep-related problems are strongly associated with the persistence of depressive symptoms in older adults [1,36-38]. Texts and videos lead the user through the modules, during which exercises are performed and homework assignments are given.

The online guided treatment for older adults from the general population includes the support of an online coach [39]. Participants receive online CBT over a period of 7 to 8 weeks. The participants are instructed to complete 1 module each week. The psychoeducation module is obligatory. We advise the participants to start with the behavioral activation and cognitive therapy modules. The problem-solving, exercise, sleep, and relapse-prevention modules are optional and are used according to the preferences of the participant. Online support for the guide consists of actively giving the participants feedback for the assignments (at the least after every completed module) using the secure messaging system included in the Moodbuster platform. Furthermore, the guide can answer any questions the participants might have.

The blended CBT treatment that will be offered to participants with moderate to severe depressive symptoms is based on evidence-based CBT protocols implemented in routine practice [40]. The blended format provides individuals face-to-face sessions and online sessions. Participants receive treatment over a period of 16 to 20 weeks, depending on the intensity of the treatment. The therapist and patient decide together the best way to organize face-to-face sessions and online sessions. For example, they can schedule an online session after each face-to-face session or an online session after 2 face-to-face sessions. The practitioner should provide feedback for the online sessions within the face-to-face sessions.

### Study Procedure

The participants will be recruited from the 2 target groups and settings simultaneously. Participants with mild to moderate depressive symptoms (as assessed with the GDS-15) [41] will be recruited from the general population via advertisements in digital media and an online recruitment platform, Link2Trials (Link2Trials BV). For this group the following steps will be taken: potential participants can express their interest by filling out a web form, after which they will receive an information letter and a printed informed consent form via postal mail. When the signed informed consent form is received, it will be scanned and safely stored at the department. Participants who sign the consent form will receive a link to the online screening questionnaires (T–1) through a secure electronic data capture (EDC) system and, once found eligible for participation, they will receive a link to the baseline questionnaires (T0) through Castor EDC (Castor Research Inc). Once the baseline questionnaires are completed, another email will be sent with login credentials for accessing the Moodbuster 2.0 platform. Participants are strongly advised to change their password upon the first login. Participants are advised to work through the intervention in 7 to 8 weeks (ie, 1 module per week). After a maximum of 8 weeks of participation, participants will receive another email with a link to another set of questionnaires to acquire posttreatment assessments (T1). After completing the posttreatment assessments, participants will receive an email to thank them for their participation and ask them if they wish to be informed about the study’s results. After filling in the last questionnaire, participants will be reimbursed for their participation with €30 (US $29.41). After the treatment has ended, the participants are invited to fill in an open-field questionnaire to evaluate their experience with Moodbuster.

Patients with moderate to severe depressive symptoms will be recruited from the patient population of the specialized mental health care outpatient clinic. For this group, the following steps will be taken: patients who express interest during intake with their therapist will receive an information letter and an informed consent form at the end of the session. Patients who sign the consent form will be assessed by their therapist to confirm they have moderate to severe depressive symptoms (as assessed with the GDS-15 [41]). Once found eligible for participation, they will receive a link to the baseline questionnaires (T0) through Castor EDC. Once the baseline questionnaires are completed, another email will be sent with the login credentials for accessing the platform. The GGZ inGeest therapists will aid participants with logging in on the platform the first time they use it. Participants are strongly advised to change their password upon the first login. Also in this step, the practitioners will assist the participants with becoming familiar with the platform and answer any questions they might have. It will also be communicated that participants should contact their therapist if they feel their symptoms are suddenly deteriorating. Participants will use the platform in a blended format. The therapists will be trained on how to use the platform before the participants start the treatment. After 16 to 20 weeks of participation (depending on the duration of the treatment), the participants will receive another email with a link to another set of questionnaires to acquire posttreatment assessments (T1). After completing the posttreatment assessments, the participants will receive an email to thank them for their participation and ask them if they wish to be informed of the study’s results. After the treatment ends, 5 participants will be invited to participate in individual interviews, which will be conducted face-to-face, through videoconferencing, or by telephone, to evaluate their experience with Moodbuster.

### Assessments

Questionnaires will be completed online for both groups. Data will be collected and managed using Castor EDC. Table 1 provides an overview of the measures employed at specific time points.

**Table 1 table1:** Measures at each assessment interval.

Questionnaires			Aim		Screening (T-1)		Baseline (T0)		Posttreatment (T1)
**Screening**									
	Geriatric Depression Scale-15	Depressive symptoms		✓					
	Item 9 of Patient Health Questionnaire-9	Suicidal ideation		✓					
**Feasibility**									
	Client Satisfaction Questionnaire-8	Acceptability/ satisfaction						✓	
	System Usability Scale^a^	Usability						✓	
	Twente Engagement with eHealth Platforms Scale	Engagement				✓		✓	
**Secondary outcome measures**									
	Patient Health Questionnaire-8	Depressive symptoms				✓		✓	
	Working Alliance Inventory—Short Form^a^	Working alliance						✓	
	Working Alliance Inventory Technical—Short Form	Technical alliance						✓	
	Uptake	Continued use						✓	
	Digital experiences	General experiences				✓			
	Digital Health Literacy Instrument	Digital literacy				✓			

^a^Measure taken from from participants and practitioners.

### Screening

#### Depression Severity

The GDS-15 [41] will be used as a screener to assess depression severity, with a cutoff between 5 and 10 for the group with mild to moderate depressive symptoms and a cutoff of 11 or higher for the group with moderate to severe depressive symptoms. The GDS-15 has 15 items with the option to respond with yes or no. Total scores range from 0 to 15, with higher scores indicating higher severity of depression. The GDS-15 has been found to be a reliable and valid instrument [42].

#### Suicidal Ideation

Participants will be screened for suicidal ideation using item 9 from the PHQ-9 [32] and excluded. Item 9 of the PHQ-9 asks about thoughts of being better off dead or hurting oneself in some way over the previous 2 weeks. Response options include 0 (“not at all”), 1 (“several days”), 2 (“more than half the days”), or 3 (“nearly every day”). A higher score indicates higher suicidal ideation. Item 9 on the PHQ-9 is a robust predictor of suicide attempts and deaths regardless of age [43].

### Primary Outcome Measures

#### Acceptance and Satisfaction

Acceptance and user satisfaction will be measured with the Client Satisfaction Questionnaire-8 (CSQ-8) for internet-based interventions [44]. The CSQ-8 is composed of eight 4-point Likert-scale items with response options ranging from 1 (“does not apply to me”) to 4 (“applies to me”). Total scores range from 8 to 32, with higher scores indicating higher levels of client satisfaction. Scores between 8 and 13 indicate poor satisfaction, scores between 14 and 19 indicate fair satisfaction, scores between 20 and 25 indicate good satisfaction, and scores between 26 and 32 indicate excellent satisfaction [45]. The CSQ-8 has been found to be a reliable instrument (Cronbach α=.87) [46].

#### Usability

Usability will be measured with the System Usability Scale (SUS), which was developed by Brooke [47], and with logfile analysis. The SUS has ten 5-point Likert-scale items with response options ranging from 0 (“strongly disagree”) to 4 (“strongly agree”). Total scores are converted (by multiplying the total score by 2.5) to a scale ranging from 0 to 100, where higher scores are indicative of higher platform usability. The SUS is considered a reliable instrument (Cronbach α=.90), with scores higher than 70 indicating “good” usability [48,49].

#### Engagement

Engagement with the platform will be measured with the Twente Engagement with eHealth Technologies Scale (TWEETS), developed by Kelder and Kip [50]. The TWEETS is a 9-item self-reported scale that can be used to measure expectations of engagement, current engagement, or past engagement with digital interventions. In the current studies, expected and past engagement will be assessed. The questions are answered on a 5-point Likert scale in which higher scores indicate higher levels of treatment engagement. The total score is derived by summing the scores for each of the 9 items on a 0 to 4 scale and can range from 0 to 40. The TWEETS has shown to be a valid tool that possesses good psychometric qualities to assess engagement with eHealth technologies (Cronbach α=.87) [51].

### Secondary Outcome Measures

#### Depression Severity

Depression severity will be assessed with the Patient Health Questionnaire-8 (PHQ-8) [52]. The PHQ-8 is composed of 8 items with response options ranging from 0 (“not at all”) to 3 (“nearly every day”). Total scores range from 0 to 24, with higher scores indicating higher severity of depression. Scores between 5 and 9 indicate mild depression, scores between 10 and 14 indicate moderate depression, scores between 15 and 19 indicate moderately severe depression, and scores between 20 and 24 indicate severe depression. The PHQ-8 has been found to be a reliable and valid instrument (Cronbach α= 0.82) [52,53].

#### Working Alliance

Working alliance will be measured using the short version of the Working Alliance Inventory–Short Form (WAI-SF) [54] which assesses the therapeutic alliance between the practitioner and participant. The questionnaire covers three dimensions of working alliance: (1) therapeutic goals, (2) tasks, and (3) bond. The WAI-SF for patients has 12 items with responses on a 5-point Likert scale, ranging from 1 (“never or rarely”) to 5 (“very often”). The WAI-SF for therapists has 10 items with responses on a 5-point Likert scale ranging from 1 (“never”) to 5 (“always”). The WAI-SF has been found to be a reliable and valid instrument for both patients and therapists (Cronbach α=.86 and α=.88, respectively) [54,55].

#### Technical Alliance

Technical alliance will be measured with the Dutch Working Alliance Inventory for Online Interventions-Short Form (WAI-TECH-SF) [56]. This questionnaire assesses the therapeutic alliance between participant and online platform. The questionnaire was designed to cover three dimensions: (1) therapeutic goals, (2) tasks, and (3) bond. The WAI-TECH-SF has 12 items with responses rated on a 7-point Likert scale, ranging from 1 (“never”) to 7 (“always”). The total score ranges from 12 to 84, with higher scores indicating a better technical alliance. The WAI-TECH-SF has been found to be a reliable instrument (Cronbach α=.97) [56].

#### Uptake

Uptake refers to the degree to which a participant engages with the content of the intervention by using or not using [57] the intervention, in this case the Moodbuster 2.0 iCBT or blended CBT. This will be measured with a logfile analysis. This analysis measures logins, time spent on the platform, and number of modules attempted and completed [58]. Additionally, for the blended CBT intervention this will be measured with feedback from the therapist on the number of face-to-face sessions attended and the number of messages sent to the participants.

#### Participant Experiences

Participants’ experiences with the platform will also be explored by means of semistructured interviews. This is to gain a better understanding of participants’ satisfaction with the use of Moodbuster. Qualitative interviews allow the participants more freedom in how to respond [59]. These interviews will focus on issues such as personal experiences with the platform, self-management strategies used by the participants, and contacts between participants and practitioners or guides. For the group with mild to moderate depressive symptoms (ie, the guided group) this will be done by means of an open-ended questionnaire after the last session. For the group with moderate to severe depressive symptoms (ie, the blended therapy group) this will be done by means of a number of individual interviews. The interviews will be conducted by telephone, by video conferencing, or be face-to-face, depending on the preferences of the participant.

### Other Measures

#### Demographic Information

Demographic information will include age, sex (as assigned at birth), living situation, educational level, relationship status, daytime activities, and whether a participant has children.

#### Digital Literacy

Digital literacy is operationalized as the degree of a person’s knowledge, comfort, and perceived skills on a digital instrument such as a computer. Digital literacy will be measured using 2 subscales of the Digital Health Literacy Instrument (DHLI), developed by van der Vaart and Drossaert [60]. The 2 subscales of the DHLI that will be used are “operational skills” and “adding content.” The operational skills subscale is composed of 3 items, with response options ranging from 1 (“very easy”) to 4 (“very hard”). Total scores range from 3 to 9, with higher scores indicating a lower degree of operational skills with digital technology. The operational skills subscale has been found to be reliable (Cronbach α=.77) [60]. The adding content subscale is composed of 3 items, with response options ranging from 1 (“very easy”) to 4 (“very hard”). Total scores range from 3 to 9, with higher scores indicating a lower degree of ability to add content on a digital tool. The adding content subscale has been found to be reliable (Cronbach α=.89) [60].

### Sample Size

Calculating the sample size for a pilot study is not standardized. Sample size can range from 15 to 100 participants and depends on the aim of the study [61]. Some studies recommend at least 12 participants [62] and other studies recommend 30 or more participants [63]. The target group from the general population is characterized by variation in both age and the nature of depressive symptoms. We will therefore recruit 30 participants from the general population. We will recruit patients receiving specialized mental health care from a smaller pool (only patients at GGZ inGeest); this population is also characterized by more severe depressive symptoms, and it will require more time to complete recruitment. Given the time frame for recruitment, we will therefore recruit 15 participants.

### Statistical Analysis

When the data collection is completed, the data will be cleaned and assessed for accuracy. The data from participants from the general population will be analyzed separately from the data from the participants that are recruited from the specialized mental health care outpatient clinic.

### Feasibility Parameters

Quantitative analysis will be conducted using SPSS (version 25; IBM Corp). The primary outcomes will only be assessed after the completion of the interventions (T1). Descriptive statistics (reported as means and SDs) will be calculated to examine and summarize the acceptance and satisfaction of the participants, system usability, and participant engagement with the platform.

### Secondary and Other Study Parameters

Descriptive statistics will be also used to assess the working alliance, technical alliance, and the participants’ use of the intervention (ie, uptake). To investigate baseline differences between participants who complete the studies and those who drop out, a 2-tailed, independent-sample *t* test or a Mann-Whitney *U* test will be used. The within-group secondary outcome of depressive severity at posttreatment will be inspected for outliers and a normal distribution. For each group, the change in depression severity pre- and postintervention will be analyzed using a 2-tailed, paired-sample *t* test with a significance level of α<.05. Effect size will be measured using Hedges *g*, and will be interpreted as follows: small (0.2), medium (0.5), and high (0.8) [64].

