**Conclusions:**

The results of these pilot studies will show whether this platform is feasible for use by the older adult population in a blended, guided format in the 2 settings and will represent the first exploration of the size of the effect of Moodbuster in terms of decreased depressive symptoms.

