## Methods

### Study Design

A single-group, pretest-posttest design will be used in both studies. Assessments will be taken at screening (T–1), at baseline (T0), and postintervention (T1). The intervention will last 8 weeks for the group with mild to moderate depressive symptoms from the general population and 16 to 20 weeks for the group with moderate to severe depressive symptoms from the specialized mental health care outpatient clinic. Written informed consent will be obtained from all participants. Figures 1 and 2 show the participant flow for both studies.

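### The paired t test on PHQ-8 uses only participants with both scores, so the change and Hedges g describe T1 responders and are biased if non-response depends on severity or improvement

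*Protocol article*

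**What the plan says.** Under Secondary and Other Study Parameters, the article names a single analysis of PHQ-8 change: "For each group, the change in depression severity pre- and postintervention will be analyzed using a 2-tailed, paired-sample". The method meant is the *t* test, two-sided at the 5% level. It adds "Effect size will be measured using Hedges" *g*, with benchmarks of 0.2, 0.5 and 0.8.

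The same paragraph foresees loss. It plans a *t* test or Mann-Whitney test "To investigate baseline differences between participants who complete the studies and those who drop out". It states no other step for people who are lost.

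Under Study Design: "A single-group, pretest-posttest design will be used in both studies". Table 1 places PHQ-8 at T0 and T1 only. The Abstract's conclusions say that the studies "will represent the first exploration of the size of the effect of Moodbuster in terms of decreased depressive symptoms", without limiting this to people who answered both questionnaires.

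**The concern.** With two time points, a paired *t* test needs both values from each person. A T0 score without a T1 score cannot enter it. The planned comparison of dropouts and completers describes selection at baseline but corrects nothing. It is also weak: at an assumed 20% loss it sets 6 people against 24 in the general-population group and 3 against 12 in the clinic group.

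Change is normally correlated with baseline, because people who start higher tend to fall further. If T1 response depends on baseline severity, the responders' mean change therefore differs from the mean change of all who started. If response depends on improvement itself, the distortion is direct. It can run either way, so a reader cannot correct for it by eye. At stake is the first published estimate of symptom change with this version of the platform. Future Directions says that the results may inform an RCT.

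**Working it through.** **No planned figure to reproduce.** The sample sizes of 30 and 15 rest on pilot-study guidance and recruitment time (Sample Size). The article gives no PHQ-8 SD, correlation, expected change or dropout rate.

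**Assumptions, not from the documents.** SD 4.5 at both time points; pre-post correlation 0.5; true mean change -4.0 points (4.0/4.5 = 0.89 SD); loss of 20% to 30%, generated by a logistic model with log-odds of 0.5 or 1 per SD of baseline or of change.

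**Formula for baseline-related loss.** Let β be the slope of T1 on T0; here β = 0.5 × 4.5/4.5 = 0.5. Then

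responders' change − true change = (β − 1) × (responders' T0 mean − all starters' T0 mean).

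The likelihood estimate is

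responders' T1 mean + β × (all starters' T0 mean − responders' T0 mean) − all starters' T0 mean,

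which removes this term.

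At 30% loss with slope 1, the simulated paired estimate is -3.43, a bias of 0.57. By the formula, responders start 0.57/0.5 = 1.14 points below all starters: -4.00 + (-0.5) × (-1.14) = -3.43.

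**Results in large samples (true change -4.0).**

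| Who is lost | Loss, slope | Paired | Likelihood |
|---|---|---|---|
| More severe at baseline | 20%, 0.5 | -3.8 | -4.0 |
| More severe at baseline | 20%, 1 | -3.6 | -4.0 |
| More severe at baseline | 30%, 1 | -3.4 | -4.0 |
| Milder at baseline | 30%, 1 | -4.6 | -4.0 |
| Non-improvers | 20%, 1 | -4.8 | -4.6 |
| Non-improvers | 30%, 1 | -5.1 | -4.9 |

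Divided by the SD of 4.5, the paired result with 30% loss of the more severe is 3.43/4.5 = 0.76, against 0.89.

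**No-change scenario.** Giving non-responders zero change multiplies the responders' change by the response proportion. At 30% loss of non-improvers, 0.7 × (-5.13) = -3.59. At 30% loss of the more severe, 0.7 × (-3.43) = -2.40. Both are smaller than the true -4.0, so this is a cautious scenario and not a corrected estimate.

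**Precision at the planned sizes (30% baseline-related loss, slope 1).** At n = 15 the standard error is about 1.45 for the likelihood estimate and 1.38 for the paired one. Root mean squared error at n = 15 is 1.45 to 1.48 against 1.48 to 1.51 across simulation runs, practically a tie. At n = 30 it is about 1.00 against 1.14. With 20% loss and slope 0.5 it is 1.30 against 1.33 at n = 15.

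**The case against.** The strongest reply is that missing-data handling is commonly left to a full protocol or SAP, and that a paired test can be run on imputed data. A missing-data section is indeed no finding here. The point rests instead on the estimator that the article names: as written, it cannot use an unpaired T0 score.

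Four stronger readings are tempting, and the document does not support them.

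- *The result is an effect in treatment completers.* Study Procedure sends T1 by elapsed time (at most 8 weeks, or 16 to 20 weeks), not on finishing modules. The general-population group is reimbursed after the last questionnaire. People who stop the modules may still answer T1.
- *The effect will be inflated, or the loss will be large.* The article foresees dropouts but gives no rate, and the direction depends on who is lost. With milder selection (20%, slope 0.5) the bias is about 0.2 points.
- *A mixed model cures the problem.* If non-improvers are lost, it moves the estimate only from -5.1 to -4.9 against a true -4.0.
- *The error will determine the size of a later trial.* No section says that this Hedges *g* will be used for that purpose, and the result is called a first exploration.

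It also stands that PHQ-8 is secondary, that an uncontrolled pre-post change already mixes any effect with natural course and regression to the mean, and that a bias of about 0.6 points lies inside a standard error of 1.0 to 1.4 points.

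**Conclusion.** The concern holds in a limited form. The paired *t* test estimates change in those with both PHQ-8 scores, while the Abstract presents the result without that limit. The estimate is biased if T1 non-response depends on baseline severity or on improvement.

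Under the stated assumptions and 20% to 30% baseline-related loss of the more severe, the bias is about 0.2 to 0.6 points on a true change of -4, and a likelihood estimate removes it. In every scenario tried, including completely random loss, the likelihood estimate had equal or lower total error. The gain is clear at n = 30 and negligible to small at n = 15. The actual size cannot be known from the document. The primary feasibility outcomes are not affected by this point. It is a modest but cheap improvement.

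**What to change.** 1. In each group, estimate the mean PHQ-8 change with a 95% CI from a linear mixed model on T0 and T1 (unstructured covariance), including everyone who starts. Base Hedges *g* on that estimate.
2. Keep the paired *t* test, labelled as the analysis of participants with both scores.
3. Add one sensitivity estimate that gives non-responders no change, reported as a cautious scenario and not as a correction.
4. State that the mixed model removes bias from baseline-related non-response but only a small part of it if non-improvers are the ones lost. Report the number with a T1 score in each group.

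The cost is analysis wording and SPSS MIXED syntax; no new data are needed. The drawbacks are a slightly larger standard error when loss depends strongly on baseline (about 1.45 against 1.38 at n = 15) and a possibly less favourable estimate.
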